# SUMMARY

**Background:**

The largest group of visual disorders after acquired brain injury are homonymous visual field defects (HVFDs). It has been estimated that 20-30% of all patients with stroke have HVFDs [1] and that 70% of these patients show a spatially disorganized visual search strategy and disturbed visual exploration of the surroundings, impairing daily mobility-related activities [2]. As a consequence, they often fail to notice relevant objects or avoid obstacles and they are often unable or afraid to walk or cycle independently. This has far-reaching, disabling repercussions on their domestic and vocational lives and participation in society. However, when patients become aware of their deficits and learn to apply a new scanning strategy in order to compensate for the visual field defect, daily life mobility may be improved substantially [3,4]. In a recently published systematic review [3], it was concluded that compensatory scanning training is the most promising approach when it comes to the level of participation in society. This training teaches patients to apply large eye and head movements towards the blind hemifield. The patient learns to enlarge the functional field of view and to compensate for the loss of visual information that would occur if no eye movements were made.

First evidence for the effects of compensatory scanning training has been found, but the training protocols that were examined differed from each other and so far, few attention has been paid to the effects on mobility. Furthermore, only studies using within-patient repeated measures designs have been performed. The randomised controlled trial (RCT) as proposed in this study protocol provides a solution for these problems.

**Aim:** The aim of this study is to examine the effect of a compensatory scanning training. The effects will be investigated on the level of functions, activities and participation. Furthermore, the predicting effects of several variables will be examined.

**Study design:** Single-blind controlled intervention study

**Study population:** Patients with HVFD (hemianopia or quadrantanopia) due to acquired brain injury, age 18-75.

**Intervention**: All participants will receive scanning training according to a protocol at Royal Dutch Visio, Centre of Expertise for Blind and Partially Sighted People.

**Primary outcome measures:** Eye movement parameters on scanning tasks (such as fixations, saccades, fixation duration, size of saccades, etc.). See *chapter 2: Objectives and research questions* for more information.

Possible risk: The effect measures do not include invasive testing. The effect measures have no adverse consequences for the participant, nor for his/her treatment at Royal Dutch Visio and there are no risks involved. Therefore, the burden is unassuming. When patients agree to participate in the study, the only thing they need to do is come to Groningen for the effect measurements on two or three separate days. Expenses for traveling and accommodation will be compensated. Patients know they can refuse or end participation in the study at any time, without any effect on their individual treatment at Royal Dutch Visio.

Additional information:

- The study is performed by Royal Dutch Visio in collaboration with the faculty GMW of the University of Groningen. Visio is responsible for implementing the training protocol and providing training. The faculty GMW is responsible for coordinating training and effect measurements.

- The interventions will be provided at several regional departments of Visio.

- The effect measurements will take place at the department of Neuropsychology of GMW located in the University Medical Center Groningen.

# 1. INTRODUCTION

The largest group of visual disorders after acquired brain injury are homonymous visual field defects (HVFDs). It has been estimated that 20-30% of all patients with stroke have HVFDs [1] and that 70% of these patients show a spatially disorganized visual search strategy and disturbed visual exploration of the surroundings impairing daily mobility-related activities [2]. As a consequence, they often fail to notice relevant objects or avoid obstacles and they are often unable or afraid to walk or cycle independently. This has far-reaching, disabling repercussions on their domestic and vocational lives and participation in society. However, when patients become more aware of their deficits and learn to apply a new scanning strategy in order to compensate for the visual field defect, daily life mobility may improve substantially [3,4]. In a recently published systematic review [3], it was concluded that compensatory scanning training is the most promising approach when it comes to the level of participation in society. This training teaches patients to apply large eye and head movements towards the blind hemifield. The patient learns to enlarge the functional field of view and to compensate for the loss of visual information that would occur if no eye movements were made.

First evidence for the effects of compensatory scanning training has been found, but the training protocols that were examined differed from each other and so far, few attention has been paid to the effects on mobility. Furthermore, only studies using within-patient repeated measures designs have been performed. The randomised controlled trial (RCT) as proposed in this study protocol provides a solution for these problems.

First of all, a detailed training protocol will be used, that will be included in the set of available training methods at Royal Dutch Visio. During the past 10 years, Visio North has built up extensive expertise of compensatory scanning training, partly based on previous PhD research in Groningen [4]. Until now, the only department of Visio experienced with this training method was located in Haren. No standardized protocol was available for this method, causing large variety in use of the method among therapists and patients. In order to recruit enough participants for the effect study, the training will be implemented throughout The Netherlands. A protocol for the training has been written by Royal Dutch Visio Haren in order guarantee unequivocality (protocol can be requested from principal investigator [name]). During the training, the patients’ awareness and understanding of the nature of their deficit is increased step by step and patients are taught to make eye movements towards the blind side with increasing size. After a number of sessions, these eye movements are combined with head movements and applied in mobility situations of increasing complexity. The goal is that after training, participation of the patients has increased by a decrease in mobility restrictions.

Second, multiple rehabilitation centers will participate in the RCT, making that the effects of training cannot be exclusively related to the expertise available within a certain region.

Third, the RCT as here proposed intends to demonstrate the effects of scanning training on several functional levels (cognitive and physiological) and multiple levels of participation and mobility.

Fourth, the effects of treatment will be examined by comparing a group of patients receiving treatment with a group of patients on the waiting list for the treatment. During this period of ‘waiting’, the latter group functions as a control group for the patients in the training stage. Allocation to one of the two groups will not affect the moment at which the training starts. In the medical-scientific literature, this method (RCT) is much more highly appreciated (class A studies) than within-patient repeated measures designs (class B or C studies).

**Relevance**

Guidance and training of mobility is one of the most frequently provided products in rehabilitation of people with a visual impairment. People with HVFD due to acquired brain injury often experience many problems on several levels of mobility. The need for an evidence-based training method improving mobility in people with HVFD is great.

In a recent systematic review by Bouwmeester, Heutink and Lucas [3], it was concluded that the effect of compensatory scanning training should be demonstrated in an RCT. This research proposal not only meets this scientific demand, but also aims at providing insight in the amount of transfer from trained strategies to practical mobility. The study as here proposed differs from previous studies on the effects of compensatory scanning training by using a wide variety of dependent variables, in order to evaluate the results of training on multiple levels. With eye tracking, it can be established whether compensatory scanning training actually leads to making larger eye movements. Psychophysiological and cognitive tasks can determine to what degree faster processing of and reacting to peripheral visual stimuli occurs after training. Mobility tests will be used to examine whether training leads to an improvement of practical mobility in and around the house or in slow-moving traffic. Subjective measures are used in order to determine whether training leads to an improvement in participation. Evaluation of compensatory scanning training on mobility has not been performed on this scale (using an RCT) before, let alone with these high-quality effect measures.

# 2. OBJECTIVES AND RESEARCH QUESTIONS

Primary:

The aim of this study is to examine the effect of a compensatory scanning training (CST). The effects will be investigated on the level of functions, activities and participation.

The expectation related to the training is that patients learn to make larger and more efficient saccades towards the blind hemifield, shifting potentially interesting objects into the functional healthy part of the visual field, enlarging the visual field of search and decreasing search time. Herewith we strive to improve general mobility, increasing participation and quality of life.

The following research questions have been defined:

*1. Does CST result in larger, more frequent and faster saccades to the blind hemifield?*

*2. Does CST result in more accurate and faster detection of peripheral visual stimuli?*

*3. Does CST result in shorter search times in complex visual environments?*

*4. Does CST result in safer participation in slow traffic?*

*5. Does CST result in less bumping to objects in complex visual environments?*

*6. Does CST result in a decrease in self-reported visual disabilities?*

*7. Does CST result in increased self-reported mobility?*

*8. Does CST result in improved self-reported quality of life?*

The order of presentation reflects the build-up of possible causal relations regarding the possible effect of the intervention.

Secondary:

Furthermore, the predicting effects of several variables will be examined.

The following aspects will be examined:

1. Visual functions, of which size of the visual field defect is the most important
2. Awareness and understanding the HVFD and its consequences in daily life.
3. Motivation for training
4. Presence of important health changes and life events during and preceding the study.
5. Premorbid level of intelligence
6. Executive functioning
7. Memory

# 3. DESIGN

The effects of scanning training will be examined by comparing a group of patients receiving treatment with a group of patients on the waiting list for the treatment. During this period of ‘waiting’, the latter group functions as a control group for the patients in the training stage. Allocation to one of the two groups will not affect the moment at which the training starts. In the medical-scientific literature, this method (RCT) is much more highly appreciated (class A studies) than within-patient repeated measures designs (class B or C studies).

Participants proceed through the following trajectory (randomised controlled trial design):

*chronology*

1. Admission stage at Royal Dutch Visio conform usual referral procedure via ophthalmology, rehabilitation or neurology.

2. Based on the available medical records, the project leaders and principal investigator decide on preliminary inclusion or exclusion. This is only possible in case the patient gives permission for exchanging medical information. Due to the standard procedures at Royal Dutch Visio, this is guaranteed for the large majority of cases.

3. In case of preliminary inclusion, assessments of visual and neuropsychological functioning are performed at Royal Dutch Visio. The patient receives a letter containing information about the study, as well as an informed consent form for agreeing with participation in the study in case the patient will be included.

4. The project leaders and principal investigator decide whether the patient is included or excluded based on the results of the assessments mentioned under 3.

5. In case the patient is included and has given informed consent, the patient is randomly allocated to the training group or control group (method of minimization, see for more information section *6.2 Selection*). Allocation to one of the two groups will not affect the moment at which the training starts. At Royal Dutch Visio, a waiting list of several months preceding treatment is not unusual. Patients from both the training group and the control group will visit the University Medical Center Groningen for a pre-assessment (the week before onset of training at Royal Dutch Visio) and a post-assessment (after 10 weeks of training). The control group will participate in a third assessment, 10 weeks before the pre-assessment (the so-called -10 assessment). By looking at the results from the pre-assessment and post-assessments of the training group and the results from the -10 assessment and pre-assessment of the control group, the effect of 10 weeks of training is compared to the effect of 10 weeks on the waiting list. In addition, the effect of treatment on the individual level can be examined by comparing the results from the post-assessment to the results from the -10 assessment and pre-assessment in the control group (within-patient repeated measures design). Including the post-assessment in the control group also increases power of the study.

In order to provide compensatory scanning training close to the patients’ residence, training will be provided at several locations of Royal Dutch Visio throughout the Netherlands, including Haren, Leeuwarden, Apeldoorn, Rotterdam and Haarlem. The final training protocol is composed in Haren. Therapists working at the participating departments of Visio received additional education in providing the training conform protocol. The training and diagnostic assessments take place at the department of Visio where the patient has registered.

# 4. STUDY POPULATION

## 4.1. Population

The study population consists of 60 patients of Royal Dutch Visio with HVFD (hemianopia or quadrantanopia, existing for at least 6 months) due to acquired post-chiasmatic brain injury. Participants have no severe motor, perceptual and neuropsychological disorders. Mobility (percentage preferred walking speed), participation and quality of life are important dependent variables in this study. These variables might also be influenced by other disorders than the hemianopia, such as severe balance disorders, disorders of cognitive functioning or psychological disorders (e.g. panic disorder with agoraphobia). There are several reasons to exclude patients with such disorders from the study. First of all, the comorbidity prevents us from determining the effect of the intervention. Second, in case of such comorbidity, other rehabilitation approaches are often preferred to the scanning training protocol. Because only severe comorbidity is excluded, the included group is expected to be sufficiently heterogeneous to determine the (predicting) influence of factors such as intelligence, memory and executive functioning on the training effect. Almost all patients with hemianopia that were registered at Royal Dutch Visio in the last couple of years had injury to the primary and/or secondary visual cortex, mostly because of an ischaemic accident in the acp or posterior part of the acm. Disorders of executive functioning, aphasia, spatial disorders and memory disorders are often related to damage to more frontal regions and are relatively rare in this patient group. Although hemiparesis is often present in the acute stage, patients with hemianopia rarely present motor problems when seen for rehabilitation at Royal Dutch Visio.

## 4.2. Inclusion criteria

- Homonymous visual field defects (quadrantanopia at minimum, three quarters affected at maximum, based on binocular Goldmann perimetry, isopters: V-4e, III-4e, I-4e, I-2e and I-1e, monocular Goldmann III-4e, and monocular Humphrey monocular 10-2), due to acquired post-chiasmatic brain injury.
- At least six months between onset of HVFD and first effect measurement
- Neurological condition is stable
- Ophthalmological condition stable for at least six months
- Age between 18 and 75 years
- Self-reported mobility-related difficulties
- Able to walk at least 50 meters independently or by using a cane/rollator, without a wheelchair (mobility assessment has to be possible, training is aimed at mobility in and around the house).
- Best corrected binocular visual acuity 0.5 (Lighthouse ETDRS 2000 chart, 4m, 500 lux, using optimal correction).
- Peak log contrast sensitivity within normal limits (Vistech VCTS6500, 4m, 500 lux, >B5 or C4)
- Eye and head mobility undisturbed in all directions
- MMSE score >25
- Sufficient memory for remembering training instructions and homework assessments (based on 8WT)

## 4.3. Exclusion criteria

- Only one functional eye
- Unclear neurological cause of HVFD
- Hemiplegia or quadraplegia
- Psychiatric disorders influencing participation, mobility and compliance with training
- Misuse of drugs/alcohol/medication
- Severe hearing impairment; hearing aids allowed, verbal communication has to be possible.
- Problems with balance or orientation impairing mobility
- Visual field defect in ‘intact’ hemi-field not connected to the main visual field defect
- Diplopia
- Metamorphosis expected to influence scanning training (Amsler test)
- Oscillopsia
- Impairments in understanding (spoken) language (based on observation)
- Severe agnosia (based on VOSP) that strongly influences the mobility problem, such as simultanagnosia
- Severe impairments of executive functioning requiring an adapted training protocol
- Severe unilateral neglect (based on Balloons, drawings, line bisection and Complex Rey Figure).
- Severe memory disorders requiring an adapted training protocol
- Strong deviance on Trailmaking, VOSP, and Balloons not explained by hemianopia
- Strong deviance on drawings and Complex Rey Figure not explained by hemianopia
- Optic ataxia
- Sticky fixation (oculomotor apraxia)

## 4.4. Sample size

The sample size was based on previous studies on the effect of CST. There is no reason to expect negative effects of training. Therefore, calculation of sample size was based on one-sided testing. Section *6.1.1 Primary outcome measures* provides more information on the reasons for eye movement parameters as primary outcome parameters. The Effect Size (ES) is calculated based on previous studies on the effect of CST on the number of fixations and refixations [2,5]. Taking the lowest value encountered (ES = 0.65), a minimum of 30 participants per group is required (training group vs. control group; two independent groups; α = 0.05; β = 0.20; one-sided testing). When comparing pre and post assessments within the total group (n=60), an ES of 0.34 can be detected with power 0.80 and one-sided testing with 0.05 significance. This means that even in case of low effectiveness of compensatory scanning training, the group size is fully sufficient. We assume an inflow of 120 patients (n=120) and we take into account a loss of 30 patients (25%) based on medical history (remaining n=90), 15 patients (17%) after assessment of inclusion and exclusion criteria (remaining n=75), and 15 patients (20%) during the period of training and effect measurements (remaining n=60).

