# 6. METHODS

## 6.1. Study parameters

### 6.1.1. Primary outcome measures

Scanning strategy based on eye tracking (fixation and saccade parameters) on a Dot Counting Task (similar to the Dot Counting Task as used by Zihl, 1995 [2]).

The order of research questions as listed in chapter *2 Objectives and research questions*, reflects the build-up of possible causal relations regarding the possible effect of the intervention. The eye movement parameters are on the base of this build-up. After all, in case the intervention would lead to an improvement in self-reported mobility and quality of life, but not to an improvement on the eye movement parameters, it would be hard to argue that the improvement can be ascribed to specific aspects of the training. A non-specific effect of training cannot be ruled out completely in a study like this, even more so because the control group does not receive a placebo intervention. This is one of the considerations to take eye movement parameters as the primary outcome in the power calculation. A second reason was that the dependent variables in the previous studies (all within-subject repeated-measures designs) on the effect of CST mainly used these eye movement parameters on visual search tasks and not questionnaires on mobility and quality of life [3]. Although these outcome parameters are of larger clinical importance than eye movement parameters, they could not be taken as primary outcome in the power calculation, because the expected effect size could not be predicted based on the literature.

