# 8. STATISTICAL ANALYSIS

Alpha=0.05 will be applied for all statistical testing.

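### The claim in Section 4.4 that the group size suffices even at low effectiveness holds only for an uncontrolled pre-post test; the randomised comparison has about 37% power at that effect size

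*Protocol*

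**What the plan says.** Section 4.4 makes two power calculations.

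- **Controlled comparison.** "Taking the lowest value encountered (ES = 0.65), a minimum of 30 participants per group is required", under these conditions: "training group vs. control group; two independent groups; α = 0.05; β = 0.20; one-sided testing". The effect size comes from earlier studies of the training, measured on numbers of fixations and refixations. Section 6.1.1 describes "the previous studies (all within-subject repeated-measures designs) on the effect of CST", and Section 1 says that "only studies using within-patient repeated measures designs have been performed".
- **Pre-post comparison.** With all 60 patients pooled, pre versus post, an effect size of 0.34 is said to be detectable with 80% power, one-sided at 0.05. The next sentence concludes: "This means that even in case of low effectiveness of compensatory scanning training, the group size is fully sufficient".

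Section 8.2 lists two analyses of the primary outcome. One compares the groups at T2, with correction for T1 left as a possibility. The other is a repeated measures analysis within the control group only. A pooled pre-post test in 60 patients is not listed. On the significance level, Section 8 says "Alpha=0.05 will be applied for all statistical testing" and does not mention sidedness.

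**The concern.** Sections 1 and 3 justify the trial by the lack of controlled evidence: only within-patient studies existed, and a randomised comparison with waiting-list patients is meant to fill the gap. Yet the assurance about low effectiveness comes from a before-after test, the type of evidence the trial was designed to improve on. A reader of Section 4.4 could take it that the randomised comparison would find an effect of about 0.34. A null between-group result might then be read as evidence that the training does not work, when that comparison would usually miss an effect of this size.

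The input to the first calculation has a related weakness. A pre-post change in uncontrolled studies includes any gain from repeating the task. The waiting-list comparison subtracts that gain. Section 6.1.1 concedes that a non-specific effect cannot be ruled out, but Section 4.4 makes no allowance for change in the controls.

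**Working it through.** **Inputs from the protocol.** n = 30 per group, ES = 0.65, one-sided α = 0.05, power 0.80; pooled pre-post n = 60, ES = 0.34 (all Section 4.4).

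**Method.** Noncentral t. For two groups of n, df = 2n − 2 and noncentrality = d·√(n/2). For a paired test, df = n − 1 and noncentrality = d·√n.

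**1. The plan's own figures reproduce.**
- Two groups of 30, d = 0.65: df 58, one-sided critical t 1.672, noncentrality 0.65 × √15 = 2.517. Power is 80.0%, so 30 per group is correct.
- Paired, n = 60, d = 0.34: df 59, noncentrality 0.34 × √60 = 2.634. Power is 83%; the smallest effect detectable at 80% is 0.325, so the stated 0.34 is slightly conservative.

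**2. The same 0.34 in the controlled comparison.**
- Noncentrality is 0.34 × √15 = 1.317. Power is 37% one-sided (25% two-sided).
- For 80% power, 108 per group would be needed one-sided (137 two-sided).
- With 30 per group, the smallest effect detectable at 80% power is 0.65 SD one-sided or 0.74 SD two-sided, without baseline adjustment.

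**3. Does T1 adjustment rescue 0.34?** The T1–T2 correlation r is not given, so it is an assumption. If 0.34 is in between-patient SD units, the effective d under ANCOVA is 0.34/√(1 − r²). If it is in SD-of-change units, the effective d is 0.34·√(2/(1 + r)).

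| r (assumed) | Between-patient SD: effective d, one-sided power | SD of change: effective d, one-sided power |
|---|---|---|
| 0.5 | 0.393, 44% | 0.393, 44% |
| 0.6 | 0.425, 49% | 0.380, 42% |
| 0.7 | 0.476, 57% | 0.369, 41% |

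Power stays below 80% on either scale.

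**4. Waiting-list gain (assumption).** If controls improve by g in the same units, the net effect is 0.65 − g.

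| g | Net ES | One-sided power |
|---|---|---|
| 0 | 0.65 | 80% |
| 0.1 | 0.55 | 68% |
| 0.2 | 0.45 | 53% |

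**5. Unknown standardiser of 0.65 (assumption).** If 0.65 is mean change divided by SD of change, with no control change, an unadjusted T2 comparison has d = 0.65·√(2(1 − r)). One-sided power for the three possible analyses:

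| r | T2 only | Change score | T1-adjusted |
|---|---|---|---|
| 0.3 | 90% | 80% | 93% |
| 0.5 | 80% | 80% | 89% |
| 0.7 | 61% | 80% | 85% |
| 0.9 | 30% | 80% | 82% |

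On this reading, power can fall below or rise above the planned 80%, depending on r and on whether T1 is used.

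**6. What the T1-adjusted analysis can detect.** Detectable difference = unadjusted value × √(1 − r²).
- One-sided, from 0.650: 0.56, 0.52, 0.46 SD at r = 0.5, 0.6, 0.7.
- Two-sided, from 0.736: 0.64, 0.59, 0.53 SD.

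**The case against.** **No number in Section 4.4 is miscalculated.** This stands. Both calculations reproduce, and the section labels the 0.34 as a pre-post figure for the total group. The fault lies in the conclusion drawn from it. Sections 3 and 6.2 say that the controls' post-assessment adds power, which suggests that a pooled analysis was in mind. Section 8.2 does not list one for the primary outcome, and even if a later plan added it, it would still have no concurrent control.

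**A reader might infer that the trial is not powered as stated.** The documents do not support that. With no waiting-list change and a change-score or T1-adjusted analysis, one-sided power would be at least 80% even if 0.65 is in SD-of-change units. Losses appear only under assumptions about retest gain, or if the T2 comparison is left unadjusted and r exceeds 0.5. The protocol gives neither the standardiser, nor r, nor the expected gain.

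**A reader might also infer that one-sided sizing contradicts Section 8.** It does not. Section 4.4 declares one-sided testing and gives a reason. Section 8 is silent on sidedness. MANOVA and mixed-design ANOVA are named in Section 8.3 for secondary outcomes, and no test is named for the between-group primary contrast. If that contrast were tested two-sided, power at 0.65 would be 70% and 39 per group would be needed. This is a reason to state the sidedness once and consistently, and it is not evidence of an error.

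**Conclusion.** The sufficiency statement in Section 4.4 is wrong for the randomised comparison. At 0.34, taken as the between-group effect size, power is about 37% one-sided, so the comparison would miss such an effect nearly two times in three. This follows from the protocol's own n, α and effect size. T1 adjustment at assumed r of 0.5 to 0.7 raises power to at most 57%.

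Separately, 0.65 is not shown to apply to the training versus waiting-list contrast, because it comes from within-subject studies and its standardiser is not stated. This makes the planning assumption unsupported without proving a shortfall. The range of 68% to 53% rests on an assumed waiting-list gain of 0.1 to 0.2 SD.

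**What to change.** **Section 4.4**
- Delete the sufficiency sentence, or limit it expressly to the uncontrolled pre-post comparison.
- State that with 30 per group the unadjusted controlled comparison has 80% power for about 0.65 SD one-sided (0.74 SD if tested two-sided), and about 37% one-sided power at 0.34.
- State that 0.65 is a pre-post effect that includes any retest gain, and say how it was standardised.

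**Section 8**
- State the same sidedness as in Section 4.4.

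**Section 8.2**
- Replace the optional T1 correction with a fixed T1-adjusted ANCOVA and base the power statement on it. At assumed r = 0.5, 0.6 and 0.7 the detectable differences are about 0.56, 0.52 and 0.46 SD one-sided, or 0.64, 0.59 and 0.53 SD two-sided.

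No extra patients are needed. The only cost is a less favourable stated figure.
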